## Abstract

**Background:**

Aboriginal and Torres Strait Islander communities in remote Australia have initiated bold policies for health-enabling stores. Benchmarking, a data-driven and facilitated ‘audit and feedback’ with action planning process, provides a potential strategy to strengthen and scale health-enabling best-practice adoption by remote community store directors/owners. We aim to co-design a benchmarking model with five partner organisations and test its effectiveness with Aboriginal and Torres Strait Islander community stores in remote Australia.

**Methods:**

Study design is a pragmatic randomised controlled trial with consenting eligible stores (located in very remote Northern Territory (NT) of Australia, primary grocery store for an Aboriginal community, and serviced by a Nutrition Practitioner with a study partner organisation). The Benchmarking model is informed by research evidence, purpose-built best-practice audit and feedback tools, and co-designed with partner organisation and community representatives. The intervention comprises two full benchmarking cycles (one per year, 2022/23 and 2023/24) of assessment, feedback, action planning and action implementation. Assessment of stores includes i adoption status of 21 evidence-and industry-informed health-enabling policies for remote stores, ii implementation of health-enabling best-practice using a purpose-built Store Scout App, iii price of a standardised healthy diet using the Aboriginal and Torres Strait Islander Healthy Diets ASAP protocol; and, iv healthiness of food purchasing using sales data indicators. Partner organisations feedback reports and co-design action plans with stores. Control stores receive assessments and continue with usual retail practice. All stores provide weekly electronic sales data to assess the primary outcome, change in free sugars (g) to energy (MJ) from all food and drinks purchased, baseline (July-December 2021) vs July-December 2023.

**Discussion:**

We hypothesise that the benchmarking intervention can improve the adoption of health-enabling store policy and practice and reduce sales of unhealthy foods and drinks in remote community stores of Australia. This innovative research with remote Aboriginal and Torres Strait Islander communities can inform effective implementation strategies for healthy food retail more broadly.

**Trial registration:**

ACTRN12622000596707, Protocol version 1.

**Supplementary Information:**

The online version contains supplementary material available at 10.1186/s12889-024-19277-0.

## Contributions to the Literature

Demonstrates what is possible in public health food retail research with established partner relationships and Aboriginal and Torres Strait Islander store directors driving change for their communityProvides a trial protocol to address a knowledge gap on effective implementation strategies for evidence-based health-enabling policy and practice in the food retail sectorPresents a novel intervention that benchmarks store businesses on best-practice policy, practice, price and purchasing metrics and uses a continuous improvement approach to support stores to  adopt best-practice Demonstrates an approach to scale health-enabling best-practice in food retail 

## Background

A unique food retail sector exists across Aboriginal and Torres Strait Islander communities in remote Australia. Over one-third of the approximate 230 stores are owned by the community and/or an Indigenous corporation [1]. Evidence is mounting of bold policy steps taken by communities to ensure their stores enable, rather than impede, health and wellbeing, despite the logistical challenges in providing a quality food supply in Australia’s most remote locations [2–8]. Aboriginal and Torres Strait Islander directors, elected by their communities to govern the community store, have increasingly exercised their power to direct policy to restrict the promotion of unhealthy food whilst promoting healthy food purchases [3–8]. Social purpose and a worldview that centres the collective, drives this unique store policy reform led by Aboriginal and Torres Strait Islander people. This is in the context of extraordinarily high rates of type 2 diabetes and related cardiometabolic chronic conditions, that to our knowledge, are among the highest in the world [9–11]. 

The health and wellbeing of society as a whole is a function of a healthy food environment [12]. Food environments across the globe have drastically altered in recent decades. Industrialisation of global and national food systems and disregard for the natural environment has enabled a growing population-level consumption of highly palatable ultra-processed foods and a concomitant rapid rise in the global burden of preventable chronic diseases [13, 14]. Many Indigenous Peoples have had their food systems irrevocably altered and/or destroyed, and with this bear a disproportionate burden of preventable chronic disease [15–17]. Indigenous Peoples continually fight to redress the systemic economic, social and political inequities associated with the structures of colonisation and marginalisation that underpin this burden [18, 19]. Improvements in diet through reduced consumption of unhealthy foods alongside increased consumption of healthy foods, could potentially prevent one in every five deaths globally [20, 21].

The 2011 report of the UN Special Rapporteur on the Right to Health submitted to the UN General Assembly recognised global food industry transnational corporations as “primary drivers of diet-related NCDs” [22]. UNICEF recently made specific recommendations for governments and the food retail industry to enact policy to restrict the promotion of unhealthy foods, particularly ultra-processed foods, recognising their detrimental impact on human and planetary health [23]. In remote Australia, Aboriginal and Torres Strait Islander community stores partnered with researchers in 2018, to generate world-first evidence that retail restriction on placement and promotion of unhealthy foods could reduce unhealthy food sales with no adverse impact on business outcomes [4]. The 7 component strategy tested included no promotion of unhealthy food and drinks, no placement of unhealthy food and drinks in high traffic areas, reduced shelf facings of targeted products (table sugar, sugar-sweetened beverages, confectionery and sweet biscuits) and no refrigerated sugar-sweetened beverages > 600 ml). In 2022, the UK Government implemented legislation to restrict the promotion of high fat, sugar and salt (HFSS) products in prominent store locations, “making a solid start towards creating healthier retail outlets for consumers” [24, 25].

Whilst there is mounting evidence to inform best-practice policy for healthy food retail, an evidence gap exists on how to implement and sustain best-practice in the food retail sector, where there is no government regulation on marketing of unhealthy food in food retail. Audit with feedback is a common strategy used in health-care delivery to promote the implementation of evidence-based practice by health care professionals and their organisations [26]. It can provide objective data on discrepancies between practice and target performance, which can increase accountability of organisations to improve quality of care and thereby increase compliance with desired practice [26]. Feedback is more effective when accompanied by both explicit goals and an action plan [27]. Benchmarking, which uses methods of audit and feedback to consider performance against a comparator, such as a peer group and/or national standards, is now used by public health researchers to increase accountability and commitment of the food industry, including manufacturers and retailers, to implement best-evidence health practice [28–30].

The Access to Nutrition Initiative (ATNI) and The International Network for Food and Obesity/non-communicable diseases Research, Monitoring and Action Support (INFORMAS) benchmarked major international and Australian food and beverage companies on their nutrition-related policies [29, 31]. Some positive changes to internal food and beverage company policies, commitments, and disclosure practices related to obesity prevention and population nutrition were reported by BIA-Obesity Australia as a result of benchmarking [32]. INFORMAS has developed a set of health-enabling best-practice performance metrics to benchmark supermarkets and has applied these in Argentina, Australia, Ghana and New Zealand [33–36]. Little is known however about the application of benchmarking in smaller and remote store settings. Further there is little known on whether benchmarking with action plans can translate best-practice evidence into policy and practice change in the food retail setting.

Continuous quality improvement employs a Plan–Do–Study–Act cycle to gather data, assess performance and system support, and set goals and strategies needed to achieve change [37]. The National Framework for Continuous Quality Improvement in Primary Health Care for Aboriginal and Torres Strait Islander People 2018–2023 emphasises the importance of organisational commitment and whole team involvement to improve systems and health care delivery by continually encouraging teams to ask ‘How are we doing?’, ‘Can we do it better?’, ‘How will we know if it is better?’ [38]. A study with four remote Aboriginal communities in Australia showed that feedback on practice performance to community store directors and their store managers with action planning as part of a continuous improvement cycle, informed change in store practice that increased fruit and vegetable sales and reduced sugar sales [39, 40]. Whilst we have this evidence, an evaluation of remote store adoption of health-enabling best-practice found there was opportunity for best-practice evidence to be better integrated in to decision-making processes [41].

Benchmarking with continuous improvement therefore provides a potential strategy to strengthen health-enabling best-practice adoption by remote community store directors/owners. The goal of the research reported herein is to co-design a model to facilitate benchmarking in the remote store setting, and test its effectiveness. We hypothesise that a codesigned benchmarking intervention can improve the adoption of health-enabling store policy and practice and reduce sales of unhealthy foods and drinks and therefore free sugars to energy purchased, in remote community stores of Australia.

This paper outlines the study protocol for the Benchmarking for Healthy Remote Aboriginal and Torres Strait Islander stores randomised controlled trial. An assessment of adoptability (including an economic evaluation) will be conducted and described separately to this paper. We use the SPIRIT 2013 Checklist: Recommended items to address in a clinical trial protocol and related documents, for this purpose, and report our research practice against The Aboriginal and Torres Strait Islander Quality Appraisal Tool designed by the Centre of Research Excellence in Aboriginal Chronic Disease Knowledge Translation and Exchange (hereafter the ‘CREATE Tool’) [42, 43]. Developers of this tool encourage its use in planning research ‘to achieve appropriate, high quality and relevant research that benefits Aboriginal and Torres Strait Islander peoples’ [43]. It emphasises the importance of Aboriginal and Torres Strait Islander leadership and partnership and is designed so that research effort reflects Aboriginal and Torres Strait Islander Peoples’ ways of knowing, being, and doing [43].

## Methods

This is a store-level pragmatic randomised parallel group, 2-arm, superiority trial with a 1:1 allocation. The study commenced in 2022.

### Our partners

Extensive and respectful collaboration with stakeholders over 30 years has informed this protocol. Consultation occurred with representatives of Aboriginal Community Controlled Health Organisations (ACCHOs), remote food retail organisations, and government, including the Arnhem Land Progress Aboriginal Corporation (ALPA), Aboriginal Medical Services Association of the Northern Territory (AMSANT), Apunipima Cape York Health Council, Health and Wellbeing Queensland, Katherine West Health Board Aboriginal Corporation (Katherine West Health Board), Miwatj Health Aboriginal Corporation (Miwatj Health), National Indigenous Australians Agency (NIAA), Northern Territory Health (NT Health), Outback Stores Pty Ltd (Outback Stores), and Sunrise Health Service Aboriginal Corporation (Sunrise Health Service). ALPA, Katherine West Health Board, Miwatj Health, NT Health, Outback Stores, and Sunrise Health Service are partners in this research.

Partners have agreed to extend the scope of their nutrition practitioners to deliver the co-designed benchmarking model with remote community stores. This workforce is on the frontline of working with communities to improve food and nutrition [44]. Nutrition practitioners with ACCHOs and government, work across multiple remote communities sometimes in a dual clinical-public health nutrition role, and support health education-type activities with stores such as group/staff education, individual store assessment/support, and cooking demonstrations [45]. ALPA and Outback Stores nutritionists are directly engaged with remote store operations and policy-making. At the time of writing this paper, ALPA has three nutritionists (including their Nutrition Manager) and Outback Stores has one (Health and Nutrition Manager).

### Study design and setting

This research is conducted in very remote Australia [46]. Most of Australia’s 7 692 024 km^2^land mass is classified as very remote with over 230 communities and a majority population of Aboriginal and Torres Strait Islander Peoples [47, 1]. These communities have a population of mostly over 250 to 1000. There are approximately eight communities of over 1000 in population and four under 250 [47]. This does not include ‘homeland’ communities or outstations that are outside larger communities and defined by the residents' cultural or traditional relationship to the land [48]. Community services generally include a school, health service, arts and cultural centre and local government council that provides essential services, and aged-care and child-care services. Most communities have a community store that that is the primary source of food for the community, with some also providing an automated teller machine, fuel depot and/or post office service [49]. Many community stores provide pre-prepared take-away meals. Large-sized communities may have more than one retail food store; most communities however are serviced by one store where residents shop, with the next nearest store a number of hours’ drive away [50].

As of 2020 16.1% of the Australian land mass is Aboriginal and Torres Strait Islander owned under ‘Aboriginal freehold land’ title through *Aboriginal Land Rights 1976 (NT) Act (ARLA)* [51–53]. This primarily occurs in the Northern Territory with 47% of the NT land mass held under Aboriginal freehold land title giving Aboriginal People of the region full ownership and rights over their land to preserve for future generations, excluding resources [52, 53]. The rights granted as part of Aboriginal and Torres Strait Islander Native title and Freehold title include collection of traditional food including hunting and fishing [54–56].

Indigenous Peoples have the right to participate in decisions that impact their lives [57]. Decisions on the type of products made available to community residents and how they are priced and promoted in-store impact health and wellbeing [58]. These decisions may be the responsibility of Aboriginal and Torres Strait Islander directors elected by the community and with a legal requirement to meet quarterly, or the responsibility of private operators depending on the business type [2]. Stores across remote Australia may be owned by the community, be privately owned where the operator has a lease agreement with the community land-owners through a lands council, and/or be government owned [2]. Community store directors may self-manage (referred to herein as independent stores) and/or contract a management service (referred to herein as store group stores) that may manage singular or multiple stores [2].

### Participants, interventions and outcomes

#### Participant eligibility criteria—inclusion and exclusion criteria

Stores located in the very remote NT of Australia that are also a primary grocery retail outlet for an Aboriginal community, and serviced by a Nutrition Practitioner with a study partner were eligible (*n* = 53 of 110 in total). Store businesses were not eligible if they did not meet the inclusion criteria and/or are a roadhouse, cafe or club (i.e., not primarily a grocery store). See Fig. 1 for SPIRIT participant flow diagram.

**Fig. 1 Fig1:**
[figure not shown]
SPIRIT Participant Flow Diagram

#### Intervention

The Benchmarking model is informed by research evidence and the best-practice ‘audit and feedback’ tools our team purposely designed for use with remote community stores, and co-designed with partners and community through two workshops (2022 and 2025), a co-design committee which includes partner representatives and other experts and meets monthly, and task groups which meet regularly [59–62].

The intervention comprises two full benchmarking continuous improvement cycles (one per year) with all stores participating in cycle 3 (Fig. 2). A cycle comprises four components (Fig. 3):

**Fig. 2 Fig2:**
[figure not shown]
Timeline of intervention

**Fig. 3 Fig3:**
[figure not shown]
The benchmarking and continuous improvement cycle of assessment, feedback, action planning and implementation. Adapted from the PLAN-DO-COLLECT-LEARN cycle, Menzies School of Health Research [63]. This figure shows the four components of the cycle and the sharing of this information with store directors/owners as represented by the middle section of the figure. Artwork by Ngarrindjeri artist [name]

Control stores receive an in-store assessment of their best-practice implementation at one time each year for three years (2022, 2023, 2024) and provide weekly store sales data (52 weeks pre to 52 weeks post intervention). They are offered a full benchmarking cycle in 2024, prior to which they will continue with usual retail practice.

*Assessment* of i) POLICY: adoption of health-enabling best-practice store policy, ii) PRACTICE: implementation of best-practice, iii) PRICE: price of a standardised healthy diet, iv) PURCHASING: healthiness of customer purchasing; v) ENVIRONMENT SCAN: Influence of enabling/impeding environment-level factors on healthy in-store operations such as disruptions to food delivery, power outages, and infrastructure.*Feedback*: Within 2-3 months of assessment, intervention stores receive a visual feedback report, with results for their Policy, Practice, Price and Purchasing indicators benchmarked against best-practice targets, all stores, and their progress over time. These reports give data-informed recommendations for performance improvement and feedback on the environmental-level factors.*Action Plan*: Partners present the feedback report to community store directors (store committee/board) in a face-to-face meeting and co-design a feasible and acceptable action plan to improve performance with the ‘who’, ‘how’ and ‘when’ described. Strategies to be employed as part of the action plan may include 'No price promotions on discretionary food and drink products', 'Price discounts on fruit and vegetables', 'No discretionary food and drink products in highly visible/high traffic areas of the store including front-of-store, check-outs, end-of-aisle caps'*Action Implementation*: The co-designed action plan is implemented by the store staff with assistance from the partners prior to the next assessment. Nutrition practitioners are encouraged to maintain regular communication with store staff to maintain motivation. Control stores receive an in-store assessment of their best-practice implementation at one time each year for three years (2022, 2023, 2024) and provide weekly store sales data (52 weeks pre to 52 weeks post intervention). They are offered a full benchmarking cycle in 2024, prior to which they will continue with usual retail practice.

#### Theory of change

Principles of Continuous Quality Improvement have informed our benchmarking model. This includes a focus on organizational process and systems, rather than on individuals within the system; the use of structured audit, feedback and action planning approaches; and, empowerment of stores to identify performance-standard gaps and action improvement opportunities [39, 40]. We draw on concepts from Feedback Intervention Theory (FIT) and goal-setting theory to consider the relationship between the Benchmarking intervention and the outcomes of improved best-practice policy and practice adoption and healthier food purchasing [69, 70]. FIT argues that feedback-standard gaps regulate behaviour by modifying the locus of attention, that then effects task learning and motivation [69]. It argues that people choose to eliminate the feedback-standard gap by attaining the standard when the goal is clear, when high commitment is secured for it, and when belief in eventual success is high [69, 70]. Our benchmarking model provides feedback to stores on their best-practice standard and target gap and their rank in performance with other stores. Through action planning, clear goals are set with stores to attain the best-practice standard.

#### Criteria for discontinuing or modifying allocated interventions for a given trial participant

There is no allowance for modifying allocated interventions. Participants (the store businesses) have the right to withdraw from the study at any time. Otherwise all consented intervention stores participate as planned in the benchmarking with continuous improvement. Implementation fidelity is monitored by the research team.

#### Strategies to improve adherence to intervention protocols

The research team provide training in the benchmarking intervention to nutrition practitioners and coaching as requested. Implementation is monitored using i. a resource-use survey (completed by nutrition practitioners after each benchmarking component, for the purpose of the economic evaluation), ii. documentation of action-plan summaries (using an excel spreadsheet), and, iii. logging of survey completions in REDCap. Interviews are conducted with partner representatives, store directors/owners and managers in 2023 and 2024 (following the Action Plan component of the cycle) to assess implementation and adoptability.

#### Relevant concomitant care and interventions that are permitted or prohibited during the trial

In this real-world pragmatic trial researchers do not have control over the practice of the participating store businesses. Data on relevant initiatives, programs, interventions that stores initiate independently to the benchmarking trial are collected through interview with store managers and through a resource-use survey in 2023 and 2024 that also collect usual practice activity.

#### Outcomes

Primary outcome: Change in the last six-months (July-December 2023) from baseline (July-December 2021) in free sugars from all food and drinks purchased (g sugar/MJ total energy), derived from electronic point-of-sale data.

Secondary outcomes: Change from baseline to i) last six months of 2022 and ii) last six-months of 2023 for the following purchasing outcomes derived from data of all food and drinks purchased:free sugars (g/MJ total energy)discretionary products weight (g/MJ total energy)core products weight purchased (g/MJ total energy)sodium (mg/MJ total energy)

Change from baseline (2022) in 2023 and 2024 in adoption of best-practice store policy action and practice implementation.

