#### Participant timeline

For intervention stores, the benchmarking cycle involves an assessment in July/August of 2022, 2023 and 2024. Feedback reports are then provided to partners for store groups and independent stores directly between October/November of 2022, 2023 and 2024. Action plan meetings are arranged by partners with stores following receipt of feedback reports in 2022 and 2023. Store directors/owners/ management then have responsibility to implement the co-designed action plans. Action implementation occurs following action plan meetings to June of each year before assessment starts again in July/August.

For control stores, data collection occurs in July/August, 2022 (using Store Scout App) and 2023 (using Store Scout App and Healthy Diets ASAP). One full benchmarking cycle will be completed, commencing with assessment in July/August, 2024.

As shown in Table 1, weekly sales data are collected from intervention and control stores from 2021 to 2025.

**Table 1 Tab1:** Summarised benchmarking performance metrics and data collection methods

Benchmark assessment area	Stores assessed	Data collector	Data collection instrument (Supplementary material)	Estimated data collection time
i) Policy: adoption of health-enabling best-practice store policy	Intervention stores (2022, 2023, 2024) Control stores in 2024	Store owner/s (for privately owned stores), store representatives or store nutritionists for stores with ALPA or Outback Stores (and with area managers for Outback Stores)	Policy Action Progress Audit e-survey: 24 three-part item survey on adoption status (full, partial, getting started, not yet started) of 21 industry- and research-informed policy actions [62]. Survey informed by research evidence, the remote food retail, government policy and health and research sectors, and BIA-Obesity, and built in REDCap [32, 64].	~ 30 min
ii) Practice: implementation of best-practice	Intervention and control stores (2022, 2023, 2024)	Trained partner nutrition practitioners/research team	Store Scout App [65]: 293 item survey on product, placement, price promotion, and product promotion in seven food/drink categories [59].	40-60 min
iii) Price: Price of standardised healthy diet	Intervention and control stores (2023/2024 only)	Trained partner nutrition practitioners/research team	Aboriginal and Torres Strait Islander Healthy Diets ASAP: on-line survey to collect food price data on 76 healthy and unhealthy food/ drink products [61].	~ 60 min

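### The primary sales window (July-December 2023) closes about six months before cycle 2 action ends and mostly before it begins, so it measures about one completed cycle, not two

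*Protocol article*

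**What the plan says.** The abstract's Methods paragraph states: "The intervention comprises two full benchmarking cycles (one per year, 2022/23 and 2023/24) of assessment, feedback, action planning and action implementation". The Intervention section repeats it: "The intervention comprises two full benchmarking continuous improvement cycles (one per year) with all stores participating in cycle 3".

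The Outcomes section sets the primary outcome as "Change in the last six-months (July-December 2023) from baseline (July-December 2021) in free sugars from all food and drinks purchased", relative to energy. The secondary purchasing outcomes use the last six months of 2022 and of 2023. Policy and practice outcomes are followed to 2024.

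The Participant timeline places intervention-store assessments in July/August of each year. It then says: "Feedback reports are then provided to partners for store groups and independent stores directly between October/November of 2022, 2023 and 2024". Action plan meetings follow receipt of the reports, and "Action implementation occurs following action plan meetings to June of each year before assessment starts again in July/August".

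On data, "weekly sales data are collected from intervention and control stores from 2021 to 2025". Control stores stay on usual practice until their own cycle, which starts with assessment in July/August 2024. Table 1 gives the Price assessment as "Intervention and control stores (2023/2024 only").

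**The concern.** The intervention is described as two full cycles, but the window used to judge it is fixed at a point where only the first has run its course. Cycle 2 reports reach stores in the fourth or fifth month of a six-month window, and its action phase continues for six months after that window shuts. No purchasing outcome is placed later.

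What is at stake is interpretation. A null result could be read as showing that two cycles of benchmarking do not change purchasing, when the sales response to most of the second was never measured. A positive result could be credited to two cycles when it came largely from one. If repeated cycles add to the effect, as feedback on progress over time suggests they might, the primary estimate would understate the effect of the intervention as defined.

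**Working it through.** **1. Calendar, from the Participant timeline and Outcomes sections.**

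| Step | Cycle 1 | Cycle 2 |
|---|---|---|
| Assessment | Jul/Aug 2022 | Jul/Aug 2023 |
| Feedback report | Oct/Nov 2022 | Oct/Nov 2023 |
| Action plan meeting | after the report | after the report |
| Action ends | June 2023 | June 2024 |

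The primary window runs from 1 July to 31 December 2023, which is 184 days. Cycle 1 action is complete when it opens. No cycle 2 feedback or action is scheduled in July-September 2023.

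**2. Bounds that need no assumption about delay.** These give the days of the window on or after the earliest possible start of action, and the share of the cycle 2 action period (to 30 June 2024) that has elapsed by 31 December.

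- Start 1 October: 92/184 = 50% of the window; 92/274 = 34% of the action period.
- Start 1 November: 61/184 = 33%; 61/243 = 25%.
- Start 30 November: 32/184 = 17%; 32/214 = 15%.

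So at most half of the window can contain cycle 2 action, and about two thirds or more of the action period falls after it closes.

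**3. Average exposure, with assumptions.** Assume reports arrive evenly over 1 October-30 November (61 days). The days x left in the window then run evenly from 31 to 92.

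- *No wait:* mean x = (31 + 92)/2 = 61.5 days; 61.5/184 = 33%.
- *Wait uniform on 0-91 days*, suggested by the quarterly meeting requirement for elected directors (Study design and setting): mean exposed days = mean of x²/(2 × 91). The mean of x² is (92³ − 31³)/(3 × 61) = 4,092, and 4,092/182 = 22.5 days; 22.5/184 = 12%. The share of stores with no exposed day is 1 − 61.5/91 = 32%.

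**4. The plan's own power figure.** The Sample size section gives 36 communities, a 3.5% difference, SD 3% and 90% power. Alpha is not stated there; I assume two-sided 5%. With 18 per arm, SE = 3 × √(2/18) = 1.00, and the noncentral t (34 df) gives 92.5%. With 17 per arm it gives 91%. The stated figure is therefore reasonable and slightly conservative.

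**5. Achieved allocation, 15 v 17 stores** (Allocation section), treated as independent. SE = 3 × √(1/15 + 1/17) = 1.063, 30 df. If a share c of the 3.5% comes from cycle 2 and a fraction f of the window is exposed to it, the effect seen is 3.5 × (1 − c + c × f).

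| c (assumed) | f | Effect seen | Power |
|---|---|---|---|
| 0 | any | 3.50% | 89% |
| 0.25 | 0.33 | 2.91% | 76% |
| 0.25 | 0.12 | 2.73% | 70% |
| 0.50 | 0.33 | 2.33% | 56% |
| 0.50 | 0.12 | 1.96% | 43% |

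The drop from 92.5% to 89% in the first row comes from recruiting 32 stores, not from the window.

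**6. Is a later controlled window available?** January-June 2024 lies within cycle 2 action, before control stores begin their cycle in July/August 2024, and within the sales data collection. January-June 2022 is its calendar match and precedes the first assessment.

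**7. Content of cycle 1.** The Intervention section lists Policy, Practice, Price and Purchasing as feedback indicators. Table 1 has no Price collection in 2022, so the one completed cycle in the window had no Price data.

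**The case against.** Three stronger readings are tempting, and the documents do not support them.

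A reader might infer that the window closes before cycle 2 is acted on at all. It does not: cycle 2 assessment and feedback fall inside it, and some stores could act in its last one to three months.

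A reader might infer that cycle 2 goes unobserved. It does not: Store Scout practice scores are collected in both arms in 2024 and described between arms. Only the purchasing response to most of cycle 2 is missing.

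A reader might infer that the trial is underpowered because of the window. The article takes the 3.5% from an earlier trial and, in the Analysis section, expects an immediate reduction of that size after retail practice change. It never describes it as the sum of two cycles. If cycle 1 delivers it, the window costs no power. The quarterly meeting rule is also a weak basis for a long delay, since it does not cover private operators, does not preclude more frequent meetings, and partners arrange the action plan meetings. This is why the power figures are shown as a range.

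Other points in the plan's favour also stand. The outcome dates are stated openly, the same-season comparison is sensible, and the hypothesis refers to a benchmarking intervention without naming a number of cycles. The Price gap is secondary, because Policy, Practice and Purchasing feedback were scheduled in cycle 1. The timeline figure is not visible to us, and an analysis plan may exist. None of this makes July-December 2023 a test of two full cycles, and the text that is visible fixes both the window and the timeline.

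**Conclusion.** The point holds in a limited form. The primary window closes about six months before cycle 2 action ends and mostly before it begins. The ceiling of 50% exposure rests only on the stated dates. The averages of 33% and 12% rest on assumed report timing and meeting delay. The primary comparison therefore estimates the effect after one completed cycle with the second under way, and no purchasing outcome covers the rest of cycle 2.

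The effect on power cannot be determined from the article. It ranges from none, at 89%, down to 43% if half of the effect comes from cycle 2 and meetings are delayed. These figures illustrate sensitivity and do not show a shortfall. The firm consequence is for what may be concluded: as planned, the sales data cannot support a statement about two full cycles in either direction.

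**What to change.** Keep July-December 2023 as the primary window, and state in the outcome and hypothesis text that it estimates the effect after one completed cycle, without Price data, with the second under way. Replacing the stated primary outcome at this stage would invite a charge of selective outcome choice.

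Before arm codes are attached to the sales data, add a declared key secondary: the same ANCOVA on January-June 2024 with a January-June 2022 baseline. State its limits. It falls during cycle 2 implementation rather than after it, and the 2022 baseline may overlap recruitment and co-design, both dated 2022 without months. Reserve any two-cycle conclusion on purchasing for that analysis.

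The cost is a dated amendment declaring an added outcome and one more run of the same model. The sales data are already within planned collection, and the sample size is unchanged.
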